## Abstract

**Background:**

Postpartum depression is a disease with a prevalence of 20% that has deleterious consequences not only for the mother but also for the baby and can cause delays in physical, social and cognitive development. In this context, the European Union Committee on Public Health has declared it essential that preventative measures are taken by centres providing care for women with a multidisciplinary approach. PROGEA is a multicentre, single-blind randomized, 3-year, longitudinal clinical trial aiming to evaluate the efficacy of a psychoeducational programme in preventing postpartum depression in at-risk women, based on a range of clinical variables, and explore prognostic factors. This paper describes the methods and rationale behind the study.

**Methods:**

We will study women receiving treatment as usual plus a psychoeducation cognitive behavioural therapy (CBT)-based intervention and a control group receiving only treatment as usual. The sample will be recruited from an incidental sampling of pregnant women in two health regions. We will recruit 600 women in the third trimester of pregnancy who consent to take part in the study. Almost half of the women, about 280, would be expected to have some risk factors for postpartum depression. All those found to have risk factors will be evaluated, and we estimate that a quarter will be classified as at-risk of developing postpartum depression as measured with the Edinburgh Postnatal Depression Scale. This subset will be randomly allocated to receive treatment as usual with or without the CBT intervention. Six sessions of CBT (1 individual and 5 group) will be offered by a psychologist.

**Discussion:**

Findings from this study will be used to design a definitive study that will examine the clinical and cost-effectiveness of the CBT-based intervention in improving the mood of women in the postpartum period.

**Trial Registration:**

ClinicalTrials.gov Identifier: NCT02323152; Date: December 2014.

## Background

Treatment of major depression is an objective of the European Union and in recent years the World Health Organization (WHO) has identified improving maternal mental health as a fundamental part of the Millennium Development Goals [1]. Today, peripartum depression (as defined in DSM-V) [2] is attracting greater attention from clinicians and researchers, as a condition that affects not only the mother, but also the health and development of the child health [3–5]; for these reasons, its prevention is particularly important [6].

The most frequent psychopathological disorders in women during pregnancy and the puerperium are depression, stress and anxiety [7]. Postpartum depression (PPD), in particular, is one of the most common complications in this period, affecting nearly 20% of all women after childbirth each year [8], but many cases go undetected and there is no international consensus on the best screening method [9].

PPD is defined as development of a major depressive episode with onset during pregnancy or within 4 weeks after childbirth and in which depressive symptoms are present for at least 2 weeks [2]. The risk factors for developing PPD include biological variables such as hormonal changes that women experience during pregnancy and after delivery; these are necessary to ensure their health during this period and are part of preparing the body for both childbirth and breastfeeding, but can cause depression in a subgroup of vulnerable women [10]. In addition to biological factors, there are psychosocial factors, among which we should highlight a personal or family history of depression or PPD and having experienced mood depression or anxiety during pregnancy [11].

Specifically, rates of PPD of more than 70% have been found in women with previous depressive symptoms [12]. Other risk factors described include: personal vulnerability of women [13], the temperament of the child [14], poor family and social support during the postpartum period [6, 15], relationship problems during pregnancy [16, 17], traumatic experiences in previous pregnancies [18] or low socioeconomic status [19].

Psychological therapy for depression has shown to be an effective treatment in depressed patients of all ages and all degrees of severity, including PPD [20]. Given the consequences of the disease, another strategy would be to administer preventive treatment with a lasting effect that could protect women against developing this type of depression. A systematic review found that 13/17 studies with successful psychological treatment targeted an at-risk population, and 4/7 trials using interpersonal therapy demonstrated success of the intervention versus a control condition [8].

The aim of this study was to identify women at risk of PPD using a protocol [21], investigate the efficacy of a structured programme of psychoeducational therapy designed ad hoc in preventing the development of PPD in at-risk women and explore prognostic factors for this type of depression.

## Methods/Design

We registered this single-blind randomized clinical trial in 2014 (identifier NCT02323152). Women will be recruited in the third trimester of pregnancy from 2015 to the completion of the study. Women that agree to participate and sign the informed consent form will then be assessed through a first screening visit by their reference midwife; specifically, the midwife will record sociodemographic data and the presence of various previously described risk factors, including the personality vulnerability of the woman and her socioeconomic status.

Women with at least one risk factor will progress to the next phase of the study and will be assessed between 8 and 15 days after the birth of their baby, at the Araba University Hospital. Clinical data will be collected relating to the delivery. We will also evaluate the women’s mood with the Edinburgh Postnatal Depression Scale (EPDS) [22], the child’s temperament with the Merrill-Palmer-Revised Scales of Development [23] and the current and overall physical activity of women with the International Physical Activity Questionnaire (IPAQ) [24] and Global Physical Activity Questionnaire (GPAQ) [25] using the Spanish versions of these tools. A score between 7.5 and 12.5 on the EPDS indicates depression risk and women with scores in this range will progress to the next phase of the study. In this phase, the participants will be randomized with Random Allocation Software 1:1 to the experimental or control group (treatment as usual). Women in the experimental group will receive six (1 individual and 5 group) sessions of the psychoeducational intervention and their status will be evaluated weekly. The control group will continue to have regular appointments with the midwife and gynaecologist and will be assessed again 6 weeks after inclusion in the trial.

We will recruit patients from five health centres in Vitoria and two health centres in Donostia, and the study is being coordinated by the Psychiatry Research team of Araba University Hospital, which is a member of the Center for Biomedical Research Mental Health Network (CIBERSAM). Patients meeting all the inclusion criteria and none of the exclusion criteria (listed below) will be included in the study.

The trial will be conducted in accordance with good clinical research practice, enabling the research to be carried out with low risk of bias and a high degree of external validity.

### Inclusion criteria

General criteria for inclusion in the 1st phase of the study:Pregnant women in their third trimester. In the case of women under 18, inclusion will be notified to the Finance MinistryWritten informed consent of the participant. In the case of women under 18, their legal representative also must sign the document.Inclusion criteria for 2nd phase of the study:Presence of one or more of the following risk factors for developing PPD, assessed in the 3rd trimester of pregnancy:Depressive or anxious symptoms during pregnancyPersonal history of severe mental disorder (schizophrenia and other psychoses, bipolar disorder, depressive disorder)Family history of severe mental disorderConcomitant medical diseases associated with depression (diabetes, heart disease, hypertension, obesity)Low or very low socioeconomic statusLack of support (partner, family, friends or others).b) A score ≥7.5 in the EPDS questionnaire when assessed 8 to 15 days after delivery. In the study of Vega-Dienstmaier et al. [22], no women with scores lower than 7.5 were diagnosed with DPP (sensitivity and positive predictive value of 100%). Therefore, we have decided to select patients with scores of 7.5 or higher on the EPDS scale.

### Exclusion criteria

Mental retardationWorsening of a severe mental disorder that could hinder understanding of the objectives of the studyLanguage difficulties that impede verbal comprehension, reading and/or writingPresence of a major depressive episode according to the DSM-IV-TR (depressive symptoms of sufficient intensity and duration longer than 2 weeks).

All participants will be informed that they will be randomized to one of the two study groups and will only be included if they give their informed consent to participate in the study. Women in both groups will be assessed at baseline (pre-intervention) and 6 weeks (post-intervention).

### Ethical considerations

The study will be conducted in compliance with local regulations and internationally established principles of the Declaration of Helsinki [26]. The study and protocol have been approved by the Clinical Research Ethics Committee of the Basque Country (Araba University Hospital: HS/PI2011013).

### Sample size

After a thorough review of the literature and using the Ene 2.0 [27] software, we calculated that for a statistical power of 90%, with a significance level of 5%, a sample of 30 patients per group will allow us to detect mean differences of 5.5 points on the EPDS between the experimental group and the control group (alpha = 0.05, beta = 0.10, *N* = 126). To achieve this sample, 600 participants in the third trimester of pregnancy will be screened for eligibility. Of the total, about 280 are expected to have at least one risk factor and will progress to the second phase of the study. Of these, we estimate that a quarter of the women will score 7.5 or higher on the EPDS, which would leave approximately 60 women to be randomized to the two arms of the trial.

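### The sample-size statement gives two incompatible sizes, 30 per group (60 in total) and N = 126, for one calculation, so 90% power for about 60 women is not established

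*Protocol article*

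**What the plan says.** The Sample size section of the protocol article contains the trial's only power statement. With power set at 90% and significance at 5%, it says that "a sample of 30 patients per group will allow us to detect mean differences of 5.5 points on the EPDS". The bracket at the end of that sentence repeats the error rates and adds a second size: "alpha = 0.05, beta = 0.10, *N* = 126".

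The section then describes recruitment. It plans to screen 600 pregnant women and expects about 280 to have at least one risk factor. A quarter of those should reach the EPDS threshold of 7.5, "which would leave approximately 60 women to be randomized to the two arms of the trial".

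Under Methods/Design, "the participants will be randomized with Random Allocation Software 1:1 to the experimental or control group", so 30 per group means 60 in total. The figure 126 appears nowhere else in the article and is not explained. The section states no SD for the EPDS and does not say whether the test is one- or two-sided.

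**The concern.** One calculation with one difference, one significance level and one power has one answer. Here it has two, and the second is 2.1 times the first (126/60). Because N = 126 stands beside alpha and beta, it reads as an output of the calculation rather than as a count of something else.

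What is at stake is how the result will be read. The Abstract says the findings will be used to design a definitive study. If 60 women really give 90% power for 5.5 points, a null result is informative about a difference of that size. If the calculation called for 126, a null result from 60 women says much less, and describing it as 90% powered could wrongly discourage the next study. An unexplained N could also be carried into that study's design.

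**Working it through.** **Inputs from the protocol article**
- Difference in mean EPDS: 5.5 points (Sample size).
- Alpha 0.05 and power 90% (Sample size). Two-sided is assumed; one-sided is also tried.
- Allocation 1:1 (Methods/Design).
- Sizes: 30 per group, and N = 126, which is 63 per group if it is a total (Sample size).
- SD: not stated. It is back-solved below only to test whether the two sizes agree. The results are not estimates of the true SD.

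**The plan's own figure.** It cannot be reproduced directly without an SD. The check is therefore which SD each size needs.

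**Step 1. Implied SD.** For two means with n per group,

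SD = difference / [(z for alpha + z for power) × √(2/n)], with 1.960 + 1.282 = 3.242.

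- n = 30: √(2/30) = 0.2582; 3.242 × 0.2582 = 0.837; 5.5/0.837 = **6.57**. The exact noncentral-t calculation gives 6.46.
- n = 63: √(2/63) = 0.1782; 3.242 × 0.1782 = 0.578; 5.5/0.578 = **9.52**. Noncentral t gives 9.45.

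The two SDs differ by a factor of √(126/60) = 1.45, so no single value serves both sizes.

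**Step 2. What each size means if the other is right.** Power ≈ Φ[difference / (SD × √(2/n)) − 1.960].

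- If 126 in total is required (SD 9.52), power with 30 per group is Φ[5.5/(9.52 × 0.2582) − 1.960] = Φ(0.28) = **61%**. Noncentral t gives 60%.
- If 30 per group is right (SD 6.57), power with 63 per group is Φ[5.5/(6.57 × 0.1782) − 1.960] = Φ(2.74) = **99.7%**, not 90%.

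**Step 3. Could an ordinary variant link the two sizes?**
- One-sided test: the implied SDs become 7.28 and 10.55, which still disagree. Power with 30 per group is about 65% if 126 is required.
- 126 read as per group: the implied SD is about 13.5, and power with 30 per group is about 35%.
- Inflation for dropout: 1 − 60/126 = 52% loss would be needed, and no loss is mentioned.
- Correction for the Mann–Whitney test: 60/0.955 = 63, or at most 60/0.864 = 70 in total.
- Recruitment counts: 126 matches none of 600, about 280 or about 60.

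None of these reconciles the figures.

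**Step 4. Power of 30 per group for 5.5 points over a range of assumed SDs** (two-sided, normal approximation; the noncentral t is up to about 1.5 percentage points lower)

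| Assumed SD | 5 | 6 | 6.5 | 7 | 8 | 9 | 9.5 | 10 |
|---|---|---|---|---|---|---|---|---|
| Power | 99% | 94% | 91% | 86% | 76% | 66% | 61% | 57% |

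**Step 5. Recruitment arithmetic.** 280 × 0.25 = 70, against approximately 60 randomised; 60/280 = 21%. The step from 70 to about 60 is not spelled out.

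**The case against.** The strongest reply is that the two figures do not have equal standing. The section moves from 30 per group to the number screened and on to approximately 60 randomised, all of it consistent with 60. Nothing is planned around 126, so a stray number is at least as likely as a real requirement. No passage supports an SD near 9.5 either. This stands, and it is why the 60% figure can only be conditional. It does not remove the contradiction, because 126 is printed as a result of the calculation and the article gives no means of setting it aside.

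It can also be said that a condensed article may leave the SD to the full protocol. That is fair, and the missing SD is not a fault by itself here. It matters only because the printed sizes disagree and the SD is what would show which one was calculated.

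A reader might infer more than the document supports:
- **That 90% power holds only with complete follow-up.** This is true only if the SD is exactly the back-solved value. At an assumed SD of 5, 21 women per group (30% lost) would still give about 94% power.
- **That the recruitment arithmetic is wrong.** Seventy counts women scoring 7.5 or higher. The Randomization section also requires that no exclusion criterion is met, and Exclusion criteria include a current major depressive episode and language difficulties. A drop from 70 to about 60 is ordinary, and the inputs are stated as approximate.
- **That 5.5 points is implausible because it exceeds the width of the 7.5 to 12.5 range in Methods/Design.** That range concerns scores at entry and does not cap a between-group difference after treatment. Inclusion criteria, Sample size and Patient assessment also give 7.5 or higher with no upper limit.

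**Conclusion.** The contradiction is real and no reading tried removes it: 30 per group and N = 126 cannot both follow from 5.5 points, alpha 0.05 and 90% power. The stated 90% power for about 60 women is therefore not established. For a two-sided comparison of means, it holds if the SD is about 6.5 or less. It is about 60% if 126 in total was the true requirement.

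A reader might go further and conclude that the trial is underpowered. The document does not support that. The SD is unknown, the rest of the section follows 60, and 126 may be a stray figure. The SDs of 6.5 and 9.5 are back-solved from the sizes and are evidence only that the sizes disagree. The point still needs correcting, because a figure in the trial's only power statement is wrong as written.

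**What to change.** - Re-run the calculation with the SD actually taken from the literature review, and state that SD, its source, the test and the sidedness. An SD back-solved from 30 per group must not be used: it would reproduce 90% by construction and justify nothing.
- Give one N. Delete N = 126, or say what it counts.
- If 126 in total was the true requirement, restate the power that about 60 women give for 5.5 points (about 60%).
- As a minor clarification, say that a quarter of 280 is 70 before exclusions, leaving about 60 to randomise.

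The cost is one recalculation and one reworded paragraph, with the possible consequence that the stated power becomes less favourable. No extra enrolment is proposed, and trial conduct does not change.

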### Patient assessment

Data on the wide range of clinical and demographic variables detailed below will be gathered using a data collection form. All candidate women will be assessed in the third trimester of pregnancy in order to screen for the presence of any of the aforementioned risk factors. Scales to assess socioeconomic status and personality vulnerability will also be administered in this screening. The next assessment will be the baseline assessment of all the women that are found to have at least one risk factor for PPD in the screening between 8 and 15 days after the childbirth. At this point, we will assess the mother’s physical activity and child’s temperament and measure the depressed mood of the mother with the EPDS. Women scoring ≥ 7.5 who are then then randomized to one of the two groups (control vs experimental) will be assessed weekly until the completion of six psychoeducational sessions, nearly 2 months after the baseline assessment. The control groups will be also re-assessed after the same interval.

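### The stated 90% power holds only with complete post-treatment EPDS data, because the 30 women per group required and the roughly 60 to be randomised are the same number

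*Protocol article*

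**What the plan says.** The Sample size section of the protocol article states that "a sample of 30 patients per group will allow us to detect mean differences of 5.5 points on the EPDS" with 90% power at the 5% level. The same sentence closes with "alpha = 0.05, beta = 0.10, *N* = 126", and the 126 is not explained. No standard deviation is given.

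The section then presents a screening funnel as the way to reach that sample. It screens 600 women in the third trimester, expects about 280 to have a risk factor, and estimates that a quarter of these will score 7.5 or more on the EPDS, "which would leave approximately 60 women to be randomized to the two arms of the trial". Methods/Design adds that "the participants will be randomized with Random Allocation Software 1:1 to the experimental or control group", so about 60 means about 30 per arm.

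The outcome comes later. Exclusion criteria places the post-intervention assessment at 6 weeks. Under Patient assessment, randomised women "will be assessed weekly until the completion of six psychoeducational sessions, nearly 2 months after the baseline assessment", and controls are re-assessed after the same interval. Data processing specifies intention to treat, meaning that women are analysed in the arm to which they were allocated.

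**The concern.** A power calculation for a comparison of means returns the number of women with an outcome. Here that number, 2 × 30 = 60, is also the expected number randomised. Every loss counted in the funnel (no risk factor, EPDS below 7.5) happens before allocation, and nothing is set aside for women who are randomised but have no post-treatment score.

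Some loss is a reasonable expectation. The women are randomised soon after an assessment 8 to 15 days after delivery and followed for 6 weeks to nearly 2 months. One arm is asked to attend six weekly sessions held only at Araba University Hospital, while recruitment also covers health centres in Donostia. Intention to treat, as defined in Data processing, fixes the arm in which a woman is counted. It does not supply a missing EPDS.

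At stake is the accuracy of the 90% figure. A reader would take it as the power of the trial as planned, when it is the power with no missing outcomes.

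**Working it through.** **Inputs from the article.** Difference 5.5 EPDS points; alpha 0.05; power 0.90; 30 per group; 1:1 allocation; about 60 randomised; funnel 600, then 280, then one quarter.

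**Inputs assumed.** The test is taken as two-sided, since the article does not say. The SD is back-solved. Loss is shown over a range and taken as equal in both arms.

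**Step 1: the plan's own figure.** Without an SD, 30 per group cannot be reproduced independently. What can be found is the SD that makes it true.
- Normal approximation: SD = 5.5 × √(30/2) / (1.960 + 1.282) = 21.30 / 3.242 ≈ 6.57.
- t-test (noncentral t, 58 degrees of freedom): SD ≈ 6.46, so d = 5.5/6.46 ≈ 0.851.

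**Step 2: power after loss.** With m = 30 × (1 − loss) analysed per arm, the noncentrality is d × √(m/2) on 2m − 2 degrees of freedom. The normal version is Φ(5.5 / (6.57 × √(2/m)) − 1.960).

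| Assumed loss | Analysed per arm | Noncentrality | Power, t | Power, normal |
|---|---|---|---|---|
| 0% | 30 | 3.30 | 90.0% | 90.0% |
| 5% | 28.5 | 3.21 | 88.4% | 88.5% |
| 10% | 27 | 3.13 | 86.6% | 86.8% |
| 15% | 25.5 | 3.04 | 84.6% | 84.8% |
| 20% | 24 | 2.95 | 82.3% | 82.6% |
| 25% | 22.5 | 2.85 | 79.7% | 80.2% |
| 30% | 21 | 2.76 | 76.8% | 77.4% |

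**Step 3: numbers that would keep 30 analysed per arm.** This is 30/(1 − loss), rounded up: 34 per arm (68 in total) at 10%, 36 (72) at 15%, 38 (76) at 20% and 43 (86) at 30%.

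**Step 4: the funnel.** 280 × 1/4 = 70, but the text gives about 60. If 70 were randomised, 60 would remain after a loss of 1 − 60/70 = 14%. The article does not call the difference of 10 an allowance for loss, and as written it falls before randomisation.

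**Step 5: sensitivity to the SD (normal approximation).** With SD 6.0, power is 94.4% at 30 per arm and 88.8% at 24 per arm. With SD 7.0, it is 86.1% and 77.7%.

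**Step 6: the other N.** If 126 were the required total (63 per group), the implied SD is 5.5 × √(63/2) / 3.242 ≈ 9.52. At that SD, 30 per arm has about 61% power with no loss at all. No single SD yields both 30 per group and 126 in total.

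**The case against.** Several objections have force.

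- **There is no cap at 60.** A reader might infer that the plan stops randomising at 60 and should be told to continue. The article does not support this. Randomization already allocates all eligible women, the 60 is a forecast of yield, and Trial status ties the end of recruitment to a date. This stands.
- **Seventy and sixty may both be right.** It is tempting to say that 70 women will be randomised and that this tolerates 14% loss. But the quarter describes women scoring 7.5 or more, and they must still pass the exclusion criteria. One of these, a current major depressive episode, bears most on high scorers. Methods/Design also gives a 7.5 to 12.5 band, which would remove higher scorers if applied. Refusals or rounding are possible too. The Abstract does describe the quarter as the subset to be allocated, with no further step, but that does not settle it. Women lost to exclusion cannot also cover later loss, so the 14% margin cannot be claimed as things stand.
- **The loss rate and SD are assumptions.** This is true, and with a smaller SD there would be slack. But the article presents 30 as the number that gives 90%, so it claims none.
- **An article may leave attrition to the full protocol.** A missing allowance alone would not be a finding. Here both numbers are printed, and the second is offered as the way to obtain the first.
- **The effect is modest.** This also stands. A reader might conclude that the trial is seriously underpowered, but on the 30-per-group figures power stays above 80% up to 20% loss. The Abstract says the findings will inform a later definitive study.

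**Conclusion.** The point holds in a limited form. The stated 90% is the power with complete outcome data, and the expected number randomised does not deliver it once any post-treatment EPDS is missing. For about 60 randomised, power is about 87%, 85%, 82% and 77% at losses of 10%, 15%, 20% and 30%. These values assume a two-sided 5% t-test, equal loss in both arms, and the SD of about 6.5 implied by the article's own 30 per group. They also assume that 30 per group, and not N = 126, is the intended calculation; if 126 was the required total, the shortfall is much larger and has a different cause. Separately, the step from 70 to about 60 is unexplained, but it cannot be called an error on the article alone. No analysis is invalidated. What is wrong is a stated operating characteristic.

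**What to change.** In the Sample size section:

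1. Say that 30 per group is the number analysed at the post-treatment EPDS.
2. State an assumed loss and give the power for about 60 randomised at that loss, for example about 82% to 87% for 20% to 10% loss, with the SD used.
3. Explain or correct the step from 280 × 1/4 = 70 women scoring 7.5 or more to about 60 randomised. If exclusions or refusals account for it, say so and keep 60. Only if it proves to be a slip should about 70 be given as the expected number, with a tolerated loss of about 14%.
4. Explain or remove N = 126 first, because the restated power depends on it.

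The randomisation rule stays as it is. The cost is a few sentences and a somewhat lower stated power, with no extra recruitment. Keeping 90% instead would not be free: at the forecast of 600/60 = 10 screened per woman randomised, 15% loss needs 72 randomised and so about 720 screened.
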